#### Secondary outcome

Occupational health knowledge will be measured by 10 questions related to organic solvents and PPE utilization. Questions were designed by the researchers according to “The usage criterion of personal protective equipment against occupational diseases in organic solvents workplace” [32] (Cronbach alpha =0.81). Correct answer for each question will achieve a score of 1, giving a total possible score of 10.Attitude towards PPE utilization. A scale of 9 items was developed by the researchers to assess migrant workers’ attitude towards PPE utilization. The scale includes four dimensions, i.e., willing of use, self-efficacy and perceived benefits and barriers (Cronbach alpha: 0.81–0.84 [20]). This measure will comprise 9 items and each will be rated on a 5-point Likert scale with ‘strongly agree’ scoring 5 and ‘strongly disagree’ scoring 1, giving an overall score ranging between 9 and 45.Participation in occupational health check-up will be measured by whether migrant workers have taken part in occupational health check-up during the past 6 months, and the number of occupational health check-ups migrant workers have received.

### Data management

To avoid missing and logic mistakes, all completed questionnaires will be checked by the interviewers immediately. Questionnaires with missing items or obvious logical mistakes (e.g. not applicable items are filled in) will be returned to migrant workers to modify. Migrant workers and SMEs who are lost to follow-up will be recorded, and the reasons for workers’ and SMEs’ drop-out will be reported by enterprise managers and local administration of work safety, respectively. Before data can be analysed, data will be processed, including correcting data-inputting errors by using double data entry method and range and logic checks.

All personal information about enrolled participants will not be shared with any third party during and after the trial to protect confidentiality. Questionnaires will be stored in a locked file cabinet in a locked room. Data will be stored in a secure database with passwords encrypted.

### Sample size

We estimate the intervention will achieve an improvement of the primary outcome, i.e., ‘rate of effective utilization of PPE during the last week’ by 43 for top-down intervention arm and 53 % for comprehensive intervention arm. According to our previous study, among migrant workers exposed to organic solvents in SMEs, the rate of effective utilization of PPE was16.8 % [10]. Based on a pilot study we did in three SMEs in Guangzhou in 2014, we expected the rate will be increased to reach 60 and 70 % in top-down and comprehensive intervention arm, respectively. Based on an estimated intra-class correlation coefficient (ICC) of 0.05(previous literature reported that ICCs for participants’ behaviours and intent to change those behaviours were generally less than 0.1 [36]), an alpha of 0.05(one-side) and a beta of 0.20, we need 684 samples and 54 enterprises. We estimated the dropout rate will be 20 % as our exploratory study showed that annual turnover rate of migrant workers exposed to organic solvents in study SMEs was 26 %. In addition, considering that SMEs are sensitive to economic depression and based on experience of local administration of work safety, we also estimated 10 % of study SMEs may close down during intervention period. Therefore, we aim to recruit a total of 60 enterprises (20 for each arm) and at least 920 migrant workers.

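### The floor of 920 workers falls about 3% short of the protocol's own 684 once both stated losses are applied; a minor arithmetic inconsistency

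*Protocol article*

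**What the plan says.** All the figures are in one paragraph of the protocol article, under Sample size.

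- Requirement before losses: "we need 684 samples and 54 enterprises".
- Worker loss: "We estimated the dropout rate will be 20" per cent, supported by a 26% annual turnover seen in exploratory work.
- Enterprise loss, introduced as a further consideration: "we also estimated 10 % of study SMEs may close down during intervention period".
- Target, presented as the consequence of these: "we aim to recruit a total of 60 enterprises (20 for each arm) and at least 920 migrant workers".

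Two statements elsewhere bear on how the target works. The Data analysis section says that missing data will not be imputed, so a worker who is lost supplies no later outcome. The Abstract says that all eligible migrant workers in the chosen enterprises will be enrolled, so 920 is a minimum and not a cap.

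**The concern.** The paragraph names two losses and offers the recruitment target as the number that allows for both. One half of the target, the enterprises, is obtained by dividing the requirement by the fraction retained. The other half, the workers, does not come out when the same method is used. If every planning assumption holds exactly and recruitment stops at the floor, the trial ends with fewer workers than the protocol says it needs.

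What is at stake is mainly the coherence of the sample-size statement, because recruitment and attrition will later be judged against it. Loss of power is a secondary matter and turns out to be very small.

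**Working it through.** **Inputs, all from Sample size:** 684 workers and 54 enterprises required (684/54 = 12.67 per enterprise); worker drop-out 20%; enterprise closure 10%; target 60 enterprises and 920 workers (920/60 = 15.33 per enterprise). The figures are read as trial totals, since the 60 enterprises are stated as a total of 20 per arm.

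**Enterprises.** 54/(1 - 0.10) = 60. The plan's figure is reproduced exactly.

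**Workers, same method.** 684/[(1 - 0.20) x (1 - 0.10)] = 684/0.72 = 950. The plan's 920 is not reproduced; the gap is 30 workers, or 950/60 = 15.83 per enterprise against 15.33.

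**Forward check.** 920 x 0.90 x 0.80 = 662.4, which is 21.6 (about 22) below 684, or 3.2%. Per surviving enterprise, 15.33 x 0.80 = 12.27 workers remain against 12.67 needed.

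**Other ways of combining the losses.**

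| Reading | Floor needed | Left from 920 |
|---|---|---|
| Separate, multiplicative | 684/0.72 = 950 | 662 |
| Added (30%) | 684/0.70 = 977.1, so 978 | 644 |
| Closures already inside the 20% | 684/0.80 = 855 | 736 |

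**Attempts to reach 920 by other routes.** 684 x 1.2 x 1.1 = 903; 684 x 1.2/0.9 = 912; 684/0.8 x 1.1 = 941; 684/(1 - 0.26) = 925, which uses the annual turnover and no closure. These lie within 3% of 920, but none equals it.

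**Effect on precision.** The ICC is 0.05 ("Based on an estimated intra-class correlation coefficient (ICC) of 0.05") and there are 54 surviving enterprises in three equal arms.

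- With 684: design effect 1 + (12.67 - 1) x 0.05 = 1.583; effective number per arm (684/3)/1.583 = 144.0.
- With 662.4: design effect 1 + (12.27 - 1) x 0.05 = 1.563; effective number per arm 220.8/1.563 = 141.2.

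At one-sided 0.05, power for 60% against 70% goes from 55.4% to 54.7%. Power for 16.8% against 60% stays near 100%.

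**Status of the base.** The 684 does not reproduce from the stated inputs ("an alpha of 0.05(one-side) and a beta of 0.20", control rate 16.8%, and "we expected the rate will be increased to reach 60 and 70 % in top-down and comprehensive intervention arm, respectively"). With the design effect of 1.583, 16.8% against 60% needs 15 x 1.583, so 24 per arm or 72 in total; 60% against 70% needs 281 x 1.583, so 445 per arm or 1,335 in total. The present point takes 684 as given.

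**The case against.** The strongest reply is that nothing practical turns on this. The floor is not a ceiling, every eligible worker is to be enrolled, and the gap is half a worker per enterprise. The number of clusters, which matters most for power here, is fully covered. All of that stands, and it keeps the point minor. It does not make the floor right: a floor should be adequate when the assumptions behind it hold, and this one is not.

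A second reply is that 20% is generous. It rests on a 26% annual turnover, while follow-up lasts 6 months. If turnover is constant, about 13% to 14% would be lost, leaving 920 x 0.9 x 0.87 = 720 or 920 x 0.9 x 0.86 = 712, both above 684. This makes a real shortfall less likely. But 20% is the planning value the protocol adopted, and the target should follow from it.

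A third reply is that the 20% may already contain closures, in which case 920 is more than enough. The paragraph introduces closure as an additional loss, so this is not the natural reading, but one clarifying sentence would settle it.

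A fourth reply is that 684 is itself doubtful. Against a requirement of 72, 662 is ample; against 1,335, both 920 and 950 fail. So correcting 920 alone does not resolve the adequacy of the sample size. That is fair, and it is why the correction should be tied to whatever base is finally kept.

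**Conclusion.** The worker target does not follow from the figures printed beside it. Taking 684 at face value, 920 leaves about 662 after both stated losses, 3.2% short, while the enterprise target is correct. The figure of 950 assumes that the losses are separate and multiply, that closing enterprises are of average size, and that the 20% applies within surviving enterprises; the range across readings is 855 to 978. The shortfall of 22 holds because the figures are read as totals.

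A reader might infer more than this, and the documents do not support it:

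- *That losses were ignored.* They were not. 920 is well above 684, and several approximate allowances for both losses land close to it.
- *That a particular slip, such as multiplying by 1.2 in place of dividing by 0.8, produced 920.* No route tried gives exactly 920, and the protocol does not show its calculation.
- *That the trial loses meaningful power through this.* The change is under one percentage point. The low power for comparing the two interventions is a separate matter, already present at 684.

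**What to change.** Make one of three changes in the Sample size paragraph, and show the calculation:

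1. Restate the floor as at least 950 workers, with 684/(0.8 x 0.9) written out.
2. Keep 920 and state that it yields about 662 evaluable workers after the assumed losses.
3. If this is what was meant, state that the 20% already includes workers lost through enterprise closure. The need is then 855, and 920 covers it.

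The cost is one number or one sentence. No procedure changes, because enrolment already takes in all eligible workers. If the base of 684 is revised, the inflation should be recalculated from the new base with both losses applied.

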### Data analysis

We will follow CONSORT guidelines [37, 38] to analyse and present the data. Intention-to-treat (ITT) analyses [39] will be used to estimate effectiveness of intervention. Therefore, all SMEs and migrant workers that are initially randomized and provide data at baseline will be included in the analysis. Migrant workers missing at baseline but present at follow-up surveys will be excluded from the ITT analyses.

The analysis will be conducted at the individual level. The baseline characteristics, e.g. demographic characteristics, occupational health knowledge and attitude and PPE utilization behaviour, of migrant workers will be described using mean (standard deviation), median (interquartile range) or proportions as appropriate and compared across three arms. Generalized estimating equations (GEE) will be used for the primary outcome adjusted for baseline PPE utilization behaviour to evaluate the effectiveness of intervention. A sensitivity analysis will be undertaken to adjust for the number of intervention sections received during the trial, which will be calculated based on general health educators, peer education group leaders and migrant workers’ feedback. In addition, subgroup analyses by migrant workers’ sex, age and education status, and SMEs’ occupational health practice, e.g. occupational health supervision, will be performed. For the secondary outcomes, linear mixed effects models will be applied for occupational health knowledge and attitude and GEE will be used for participation in occupational health check-up. Results from all secondary analyses will be treated as exploratory and presented as estimates with confidence intervals.

Although drop outs are expected, missing data will not be imputed. Because GEE and linear mixed effects models assume that missing data are missing at random. Under this assumption, the complete-case analysis by including predictors of missing observations will provide consistent estimates of the parameter [40].

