### Study interventions

The preliminary intervention plan was designed based on our previous exploratory study [20] and literature review on behavioural change theory and influencing factors of PPE utilization behaviour (Fig. 1). A qualitative study was then conducted in three SMEs to 1) provide details about the mechanisms through which individual and organizational factors affect the target behaviour; 2) understand the feasibility and acceptability of the proposed intervention; and 3) seek the suggestions of occupational health personnel and migrant workers on improving the intervention. Based on the interview results, the intervention plan was revised and finalized. We will test the effectiveness of intervention in three arms:***Intervention arm 1*****:** A top-down intervention including:Occupational health education towards managers and occupational health personnel in each enterprise will be accomplished in the first week of intervention. The education will focus on enterprises’ responsibilities on occupational health; and benefits they will gain by creating a healthy workplace and improving workers’ health; as well as activities they could take to achieve the goal, e.g., providing appropriate PPE and establishing and enforcing a supervision plan. The education will be organized by local administration of work safety and delivered by trained educators.General health education: One lecture on PPE utilization will be organised among migrant workers in the first week of intervention. The lecture will focus on the introduction of organic solvents, dangers of not using PPE, and how to properly select, use and store of PPE. The education in each SME will be delivered by two trained educators as a team. In addition, related brochures and posters will be delivered to migrant workers at baseline and 3-month follow-up of intervention.mHealth intervention: PPE utilization and other related occupational health messages will be sent twice a week through Instant Message Apps, including WeChat, Tencent QQ and Fetion, depending on which App is more commonly used by each migrant worker.***Intervention arm 2*****:** A comprehensive intervention, including:The same intervention as that in the intervention arm 1;Peer education will be organised once a month. Each peer group will include 8–15 migrant workers and one of them will be assigned as a group leader based on the voluntary principle. Group leaders will receive a course on peer education and a handbook designed by the research team (WC, XL and SF), as well as establish contact with our project coordinators (TL, FZ, SH and JS) to send feedback and get help timely. The overall 6 monthly peer educations will be launched by group leaders for no longer than 60 min each time. The intervention will begin with an ice-breaking game and introduction of peer education in the 1st month, followed by organic solvents and the related protection education in the 2nd month, how to use PPE and personal experiences of benefits and barriers of use PPE in the 3rd-5th months, and maintenance of PPE utilization in the 6th month. In addition, group leaders will be asked to monitor other group members’ PPE utilization behaviour in the workplace. Every month, all group leaders will receive 50 RMB (8 $USD) and the top five best performing leaders will receive additional 50 RMB as a token of appreciation.***Control arm*****:** In the control arm, we do not provide any intervention, neither on the enterprises nor on the migrant workers. Occupational health circumstances at the workplace will be as usual.

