### Intervention fidelity

To maintain the quality of intervention delivery and track fidelity to the intervention, we will collect information from general health educators, peer education group leaders and migrant workers, respectively. First, general health educators will be asked to submit a written implementation form recording the adherence to protocol and photos via email to project coordinators as soon as the education was over. Second, at the end of each month, peer education group leaders will also be asked to submit an implementation form and photos to project coordinators to report the adherence to protocol, barriers to the implementation of peer education and their suggestions. PI, Co-PI and project coordinators of this project will look over these forms and provide feedback to all group leaders each month. Third, migrant workers’ self-reported adherence to the intervention, including the number of mHealth messages received each week, the number of education sections attended every month and their satisfaction, will be collected by the two follow-up questionnaire surveys.

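### The planned adjustment for number of sessions received conditions on part of the randomised treatment, so it cannot test the robustness of the intention-to-treat effect

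*Protocol article*

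**What the plan says.** The Data analysis section sets intention-to-treat as the principle and names the primary model: "Generalized estimating equations (GEE) will be used for the primary outcome adjusted for baseline PPE utilization behaviour to evaluate the effectiveness of intervention". The next sentence adds the analysis at issue: "A sensitivity analysis will be undertaken to adjust for the number of intervention sections received during the trial". The count is to be built from the feedback of educators, peer leaders and workers.

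The Study interventions section fixes how many sessions a worker can receive:

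- Control: "In the control arm, we do not provide any intervention, neither on the enterprises nor on the migrant workers".
- Top-down: "One lecture on PPE utilization will be organised among migrant workers in the first week of intervention". Twice-weekly messages, brochures and posters come on top, and managers receive separate education.
- Comprehensive: everything in the top-down arm, plus peer education. "The overall 6 monthly peer educations will be launched by group leaders for no longer than 60 min each time".

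The Intervention fidelity section has workers report "the number of education sections attended every month" in the two follow-up surveys, so attendance is recorded only after randomisation. It lists messages separately from education sections.

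**The concern.** A sensitivity analysis of the primary result should estimate the same effect under different assumptions. This one changes the effect. Sessions are the means by which much of the intervention is delivered, so holding them constant across arms removes part of what was randomised.

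Workers who attend more may also be those more inclined to wear a respirator. The count then brings in confounding that randomisation had excluded.

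The comparison most exposed is one of the trial's two stated aims: whether the comprehensive intervention beats the top-down one. Those arms differ by peer education, and peer sessions make up most of the count. A sound positive intention-to-treat result could be followed by an analysis, labelled as a check on it, that appears to contradict it.

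**Working it through.** The plan gives no figure for this analysis, so there is none to reproduce. The check has a structural part and two simulations.

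**Structure.** Possible counts, leaving messages out, are 0 in control, 0 to 1 in top-down, and 0 to 1 + 6 = 7 in comprehensive. A control worker cannot have a non-zero count, and a top-down worker cannot have more than 1. Any comparison at a common count above 1 is extrapolation.

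**Unadjusted effects at the planned rates** (Sample size section: 16.8%, 60%, 70%):

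- Odds: 0.168/0.832 = 0.202; 0.60/0.40 = 1.50; 0.70/0.30 = 2.33.
- Comprehensive vs top-down: 2.33/1.50 = 1.56.
- Top-down vs control: 1.50/0.202 = 7.4.
- Comprehensive vs control: 2.33/0.202 = 11.6.

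**Simulation 1: sessions have no causal effect.** Everything about attendance is assumed. Motivation u is standard normal. The log-odds of PPE use rise by b per SD of u, with intercepts set to give the planned rates. The probability of attending each session is expit(0.8 + c·u), about 0.67 on average. A logistic model is fitted with and without the session count, in a very large sample without clustering or the baseline covariate.

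| b (PPE use) | c (attendance) | Adjusted OR, comprehensive vs top-down |
|---|---|---|
| 0.9 | 0.8 | 0.37 to 0.39 over repeated runs |
| 0.5 | 0.8 | 0.68 |
| 0.5 | 0.4 | 0.83 |
| 0.3 | 0.3 | 1.13 |
| 0 for either slope | any | essentially unchanged, about 1.55 |

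In the first row, comprehensive vs control falls to about 2.2 and top-down vs control to about 5.8.

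The comprehensive vs top-down contrast is fragile for a simple reason. The adjusted log odds ratio is roughly the unadjusted one minus (slope per session × difference in mean sessions). The difference is about 6 × 0.67 = 4.0 sessions, and ln 1.56 = 0.44. A slope of 0.44/4.0 = 0.11 per session, an odds ratio of 1.12, is enough to erase the contrast.

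**Simulation 2: closer to the planned model.** There are 20 enterprises per arm and 15 workers per enterprise, with ICC 0.05. The model is a logistic GEE with exchangeable correlation and baseline PPE use as covariate, with 100 runs per scenario. Attendance is 80% for an average worker and varies with motivation. Where motivation also affects PPE use, the effect is 0.5 log-odds per SD. Entries are mean log odds ratios, without → with the session count.

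| Scenario | Top-down vs control | Comprehensive vs control | Comprehensive vs top-down | Last contrast negative after adjustment |
|---|---|---|---|---|
| (a) Effect wholly through sessions, no confounding | 1.86 → 1.40 | 2.20 → −0.94 | 0.34 → −2.34 | 100% of runs |
| (b) As (a), with confounding | 1.81 → 1.21 | 2.11 → −2.03 | 0.30 → −3.24 | 100% |
| (c) No session effect, with confounding | 1.84 → 1.66 | 2.26 → 1.04 | 0.43 → −0.62 | 95% |
| (d) Neither | 1.94 → 1.94 | 2.38 → 2.38 | 0.44 → 0.44 | 11% |

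In (d) the estimates hold, but the standard error of the comprehensive coefficient doubles (ratio 2.03). Arm alone explains 73%, 87% and 94% of the variance in sessions at 60%, 80% and 90% attendance. At 60% and 90% the comprehensive vs top-down contrast is again negative on average in (a) to (c) and positive in (d). Top-down vs control shrank in (a) to (c) but never changed sign.

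**The case against.** Several points count on the other side.

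- **The primary inference is untouched.** Effectiveness is judged by the intention-to-treat GEE without the count. Harm arises only if a supplementary result is misread. This stands and limits the severity. The section also treats secondary analyses as exploratory, but it is unclear whether that covers a sensitivity analysis of the primary outcome.
- **The model is described in one sentence.** It does not say that all three arms enter one model, that the count is linear, or that the arm coefficient is what will be reported. A fuller document may settle this. Coming straight after the primary model, the plain reading is still the arm comparison with the count added. The point is conditional on that reading.
- **A reader might infer that the adjusted coefficient is meaningless or must reverse sign.** The documents do not support either. With no session effect and no confounding it is unchanged and only less precise. If sessions carry the effect, it resembles a direct effect, though a confounded one. It answers a different question from the intention-to-treat effect.
- **The size rests on assumptions.** The article reports no attendance or motivation data, and the weakest confounding tried (0.3 and 0.3) gives no reversal. Only a range can be given.
- **Sections might include messages.** The Intervention fidelity section lists them apart, which argues against this. If about 48 messages (two a week for 24 weeks) are counted, comprehensive vs top-down did not reverse in a trial run (odds ratio 1.17), but both arms fell below 1 against control. The objection then takes another form.
- **A reader might infer that the count is missing for every drop-out.** Educator and peer-leader forms also feed it, so that is not claimed here.

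**Conclusion.** The point holds in a limited form. On the plain reading, the session-adjusted arm coefficient does not estimate the intention-to-treat effect, so neither agreement nor disagreement with the primary result says anything about robustness.

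This follows from the design and needs no assumption about attendance. The size does need one. With no causal session effect, the comprehensive vs top-down odds ratio of about 1.55 moves to somewhere between 0.37 and 1.13 as assumed confounding goes from strong to weak, and stays put with none. Reversal is also possible when the effect acts through sessions. It is a real possibility, chiefly for contrasts involving the comprehensive arm, and not a certainty.

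The primary analysis stands as planned. The sentence should be changed, but the fault does not threaten the trial's main conclusion.

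**What to change.** Replace the one sentence in the Data analysis section. Do not enter session count as a covariate in a model that compares arms, and do not present such a result as a sensitivity analysis of the intention-to-treat effect.

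Use the count in a dose-response analysis within each intervention arm separately, with enterprise-clustered errors, labelled exploratory and observational. State whether messages count as sections.

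A complier-average estimate with randomised arm as instrument is an option only if adherence is defined on the whole intervention package and the exclusion assumption is stated. Manager education, posters, messages and monitoring by peer leaders can all act on a worker who attends nothing, so session count alone would strain that assumption.

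The cost is a reworded sentence and a little more analysis, using data already to be collected. The drawback is that the within-arm result has no causal reading.

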### Outcome measures

The questionnaire data will be collected at baseline, 3th month follow-up and the end of intervention respectively. Baseline data will be collected prior to the research team starting the intervention. The three surveys will be carried out in both the intervention and control arms and organised with the help of enterprise mangers.

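### The knowledge, attitude and check-up models name no baseline term, unlike the primary model; stating one is a free gain in precision

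*Protocol article*

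**What the plan says.** All the model statements are in one paragraph of the protocol article's Data analysis section. For the primary outcome: "Generalized estimating equations (GEE) will be used for the primary outcome adjusted for baseline PPE utilization behaviour to evaluate the effectiveness of intervention". The statement on knowledge, attitude and check-ups reads: "linear mixed effects models will be applied for occupational health knowledge and attitude and GEE will be used for participation in occupational health check-up". The second sentence gives a model class for each outcome but no covariate, time structure or contrast.

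The baseline values are available. Under Outcome measures: "The questionnaire data will be collected at baseline, 3th month follow-up and the end of intervention respectively". The analysis set is limited to enterprises and workers that were "initially randomized and provide data at baseline will be included in the analysis". Knowledge and attitude are among the baseline characteristics to be described and compared across the three arms ("The baseline characteristics, e.g. demographic characteristics, occupational health knowledge and attitude and PPE utilization behaviour, of migrant workers"). Check-ups are not named there, but that list is given as examples.

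On the standing of these analyses: "Results from all secondary analyses will be treated as exploratory and presented as estimates with confidence intervals".

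**The concern.** The article took the trouble to write a baseline covariate for one outcome and wrote none for the others a few lines later. An analyst working from this text could fit the secondary models without baseline and be following the plan.

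Knowledge and attitude matter here, because the first stated objective sets them beside PPE behaviour. Only 20 enterprises are randomised to each arm, and the Randomisation section describes no stratification, so visible baseline differences between arms can arise by chance. The plan compares knowledge and attitude across arms at baseline but does not say what follows if they differ. Whether to adjust could then be decided after the data are seen. What is at stake is the width of the published intervals and the handling of chance baseline differences between arms, not the validity of the comparison.

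**Working it through.** The article states no precision or sample size for the secondary outcomes, so there is no figure of its own to reproduce.

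**Inputs from the article (Sample size section).** 60 enterprises, 20 per arm; at least 920 workers; 54 enterprises and 684 workers before allowance for losses; ICC 0.05, with behavioural ICCs said to be generally below 0.1.

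**Assumptions.** The ICC was set for the primary outcome and is carried over to the secondary ones. The article gives no SD and no baseline-to-follow-up correlation for knowledge, attitude or check-ups, so results are in SD units and shown over a range.

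**Step 1: chance baseline difference between two arms.**
- Workers per enterprise: m = 920/60 = 15.33. Workers per arm: 20 × 15.33 = 306.7.
- SE = sqrt(2 × (1 + (m − 1) × ICC) / 306.7).
- ICC 0.05: sqrt(2 × 1.717 / 306.7) = 0.106 SD, 95% range ±0.21 SD.
- ICC 0.10: sqrt(2 × 2.433 / 306.7) = 0.126 SD, 95% range ±0.25 SD.
- With 54 enterprises and 684 workers, ICC 0.05: m = 12.67, design effect 1.583, SE = sqrt(2 × 1.583 / 228) = 0.118 SD.

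**Step 2: baseline as covariate against follow-up values only.** The SE ratio is sqrt(1 − r²), taking the correlation r to be similar for workers and for enterprise means.

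| Assumed r | SE ratio | Reduction in SE |
|---|---|---|
| 0.3 | 0.95 | 5% |
| 0.5 | 0.87 | 13% |
| 0.7 | 0.71 | 29% |

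**Step 3: baseline carried as a repeated response instead.** Worked example with 18 enterprises per arm, 13 workers each and ICC 0.05, assuming a within-worker correlation of 0.5 and a correlation of enterprise effects between surveys of 0.8.
- Variance of an enterprise mean: 0.05 + 0.95/13 = 0.1231.
- Covariance of its baseline and follow-up values: 0.8 × 0.05 + 0.5 × 0.95/13 = 0.0765. Correlation of enterprise means: 0.0765/0.1231 = 0.62.
- Follow-up only: SE = sqrt(2 × 0.1231/18) = 0.117.
- Baseline as covariate, or as a response with a common mean across arms: 0.117 × sqrt(1 − 0.62²) = about 0.092.
- Arm-by-time contrast with separate baseline means: 0.117 × sqrt(2 × (1 − 0.62)) = about 0.102.

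In this example adjustment gives an SE 21% below follow-up only (0.092/0.117 = 0.79) and 10% below the arm-by-time contrast (0.092/0.102 = 0.90). It gives nothing beyond a common-mean model. The middle case depends on the correlation: sqrt(2(1 − r)) exceeds 1 when r is below 0.5, and an arm-by-time contrast is then less precise than follow-up values alone. A 150-replicate simulation under the same values gave 0.118 for follow-up only and 0.092 with the covariate. Some of those fits gave convergence warnings, but the results agree with the formulas.

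**Step 4: check-ups.** The item asks "whether migrant workers have taken part in occupational health check-up during the past 6 months". At the 3-month survey about three of those six months lie before the intervention, inside the window already covered at baseline. One check-up can therefore count in both covariate and response. This does not bias the comparison, because the covariate is measured before the intervention. The figures in Step 2 do not carry over directly to a binary outcome, and under a logit link adjustment changes the odds ratio being estimated.

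**The case against.** The strongest reply is that silence is not exclusion. The sentence names a model class and nothing else, and covariates for exploratory secondary models are often left to a full protocol or analysis plan, which is not shown. A mixed model or a GEE over all three surveys can hold baseline in the response. The missing-data paragraph also foresees extra covariates ("the complete-case analysis by including predictors of missing observations will provide consistent estimates of the parameter"), and baseline values could enter there. All of this stands. It is why the loss can only be called possible, and why the point asks for a sentence and does not allege an error.

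A reader might infer more than the text supports:

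- **That the planned models leave baseline out, and that the check-up GEE cannot use it.** The article says neither. A GEE with baseline in the response and arm-by-time terms would use it.
- **That unadjusted estimates are biased.** Randomisation keeps them unbiased, and an interval that allows for clustering already includes chance differences between arms.
- **That adjustment is worth a large number of extra workers.** At r = 0.7 the variance falls by 49%, which suggests 96% more workers (1/0.51 = 1.96). With the number of enterprises fixed that is wrong: at ICC 0.05, 96% more workers takes ICC + (1 − ICC)/m from 0.112 to 0.082, a cut of about 27%.

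The exploratory label lowers the stakes but does not remove them, since estimates with intervals will be reported. What the reply leaves standing is that the article states the baseline term for one outcome and not for the others, when the data for it are already collected.

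**Conclusion.** The point holds as one of precision only. The article fixes baseline adjustment for the primary outcome and names no baseline term for knowledge, attitude or check-ups. Followed literally, the secondary comparisons remain valid but may be less precise than the collected data allow, and they leave unadjusted a chance difference between arms whose SE is about 0.11 SD at ICC 0.05. Against follow-up values alone the SE would be about 5% to 29% smaller for correlations of 0.3 to 0.7. If baseline is already a response with a common mean, nothing is lost.

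The sizes rest on correlations that the article does not give and on an ICC borrowed from the primary outcome. They describe the two continuous scores better than the binary check-up outcome. This is a free improvement to exploratory analyses and does not threaten the trial's main conclusion.

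**What to change.** Add one statement to the Data analysis section, before any outcome data are analysed: each secondary model takes the 3- and 6-month values as response and includes the worker's baseline value of the same outcome (knowledge score, attitude score or check-up status) as a covariate, as for the primary outcome, with clustering by enterprise. For the two continuous scores, baseline as a repeated measurement with a common mean across arms is an equivalent choice; name whichever is used.

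For check-ups, add two notes: that the look-back at 3 months overlaps the baseline window, and, if a logit link is used, that the reported odds ratio is adjusted for baseline status and so differs from the unadjusted one.

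The cost is one covariate per model. Workers without baseline data are already excluded, and the Data management section returns questionnaires with missing items for completion, so few if any workers should be lost and no further data are needed.
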